## Abstract

**Background:**

The reporting of adverse drug reactions (ADR) by patients represents an interesting challenge in the field of pharmacovigilance, but the reporting system is not adequately implemented in France. In 2015, only 20 MS patients in France reported ADR due to first-line disease-modifying drugs (DMD), while more than 3000 patients were initiated on DMD.

The aim of this study is to validate a proof-of-concept as to whether the use of a mobile application (App) increases ADR reporting among patients with relapsing-remitting multiple sclerosis (RR-MS) receiving DMD.

**Methods/design:**

We designed a multi-centric, open cluster-randomized controlled trial, called the Vigip-SEP study (NCT03029897), using the App My eReport France® to report ADR to the appropriate authorities in E2B language, in accordance with European regulations. RR-MS patients who were initiated on, or switched, first-line DMD will be included. In the experimental arm, a neurologist will introduce the patient to the App to report ADR to the appropriate French authorities. In the control arm, the patient will be informed of the existence of the App but will not be introduced to its use and will then report ADR according to the usual reporting procedures. Primary assessment criteria are defined as the average number of ADR per patient and per center. We assume that the App will increase patient reporting by 10-fold. Therefore, we will require 24 centers (12 per arm: 6 MS academic expert centers, 3 general hospitals, 3 private practice neurologists), allowing for an expected enrollment of 180 patients (alpha risk 5%, power 90% and standard deviation 4%).

**Discussion:**

Increasing patient reporting of ADR in a real-life setting is extremely important for therapeutic management of RR-MS, particularly for monitoring newly approved DMD to gain better knowledge of their safety profiles. To increase patient involvement, teaching patients to use tools, such as mobile applications, should be encouraged, and these tools should be tested rigorously.

**Trial registration:**

ClinicalTrials.gov, ID: NCT03029897. Registered on 20 January 2017.

**Electronic supplementary material:**

The online version of this article (10.1186/s13063-018-2560-4) contains supplementary material, which is available to authorized users.

## Background

Adverse drug reactions (ADR) constitute some of the major causes of morbidity and mortality worldwide. It is estimated that ADR account for more than 5% of hospital admissions, 28% of emergency department visits and 5% of deaths during hospitalization [1]. Thus, ADR caused approximately 200,000 deaths per year in Europe and generated costs of 79 million euros in 2015 alone [2].

Spontaneous reporting of ADR is the backbone of the pharmacovigilance system and has been proven to play a role in identifying signs related to drug safety. Descriptions of the safety profiles of drugs during clinical development are not exhaustive and do not reflect potentially late or rare occurrences of ADR [1]. Spontaneous reporting by health care professionals in subsequent post-marketing settings is the greatest source of drug safety data [3]. However, under-reporting of ADR is a key limitation of the efficiency of pharmacovigilance systems, and spontaneous reporting by patients is now recognized as a new source of information for these systems.

A recent review of the academic literature confirmed that patient reporting adds new information about ADR: such reporting provides a more detailed description of ADR that differs in terms of the nature of the reaction and the suspected drugs involved [4]. In the Netherlands from 2010 to 2015, patients made important contributions by reporting 26% of all ADR reports [3, 5]. The Danish Medicines Agency published a report on ADR reported by consumers compared with reports from health care professionals covering the period from 2003 to 2011 and showed that consumer reports contribute significantly to the total number of ADR reports, both quantitatively and qualitatively [6]. Patient self-reporting was also investigated in the United Kingdom (UK) in the UK’s Yellow Card Scheme from 2005 to 2007, and the results also suggested that patient reporting provides a positive complementary contribution to health professional reporting [7, 8]. In France, during the pandemic influenza vaccination campaign in 2009–2010, a pharmacovigilance plan was introduced following the recommendations of the European Medicines Agency (EMA). For the first time in France, patients were able to report ADR concerning the pandemic vaccine directly to pharmacovigilance centers. This study revealed no major qualitative differences between patients’ and health professionals’ reports [9]. Despite growing interest and acceptance of ADR reporting by patients [10, 11], few studies have validated the relevance of data from patient notifications [12–14].

Health authorities in 44 countries currently emphasize spontaneous ADR notifications by patients and the need for a more accessible reporting system [15]. According to new European legislation (Directive 2010/84/EU), member states are required to establish an ADR reporting system for patients. Since 2011, patients in France have been able to self-report their ADR without involving a health professional. The French pharmacovigilance system is based on 31 regional drug monitoring centers and a dedicated unit of the French Agency “Agence nationale de la sécurité du médicament et des produits de santé (ANSM).” Patients can report ADR either directly to ANSM via a form that is available at http://ansm.sante.fr/ or to a regional center electronically or by telephone. However, patient reporting in France remains underdeveloped, and its availability is not widely known by the general population [16]. For example, in 2014, ADR reported by patients represented 4.5% of all reports, compared with 10% in Europe, according to data from the French National Database of Pharmacovigilance [16]. Most patients remain unaware of reporting systems or are confused about reporting [17].

Therefore, “e-health” applications could be a convenient method to more closely connect with patients [18]. It has been demonstrated that the use of mobile applications to report adverse events, such as those related to a medical device, can save time and increase the number of notifications. On average, there were 15 times more reports submitted per month via the App MedWatch® with patient community support than submitted via traditional pharmacovigilance portals [19].

In 2016, it was estimated that 50% of the population and 99% of young physicians in France own a smartphone. The most widely used medical Apps by young physicians are Apps related to drugs (drug database, drug interaction database) [20]. A smartphone/tablet application seems to be a necessity for modern pharmacovigilance approaches (i.e., MedWatcher® in USA or YellowCArd® in UK).

In France, several applications dedicated to ADR reporting are available on the market (i.e., VigiBip®, My e-Report®, Medisafe®), but these applications are not yet widely used by patients. For example, in the Toulouse University Pharmacovigilance Center, patient reports submitted by the App VigiBip® (6.7% of total reports received by the center) were significantly more frequent than those submitted via classical methods (3.4%) (*p* = 0.01) [21].

To further promote patient involvement, teaching tools, such as mobile applications, should be encouraged, and these tools should be tested rigorously.

### Population

During the past years, different new disease-modifying drugs (DMD) have become available on the market for multiple sclerosis (MS) care, although most of these drugs induce significant general and biological side effects. While these new treatments offer important medical benefits, they also require close monitoring, which has led to the implementation of risk management plans (RMP). Clinical trial populations are homogenous and rigorously followed, whereas under-reporting by patients is undeniable in normal clinical practice.

Hence, increasing the rate of spontaneous reports of ADR by MS patients would represent a significant contribution to the pharmacovigilance system. MS occurs in young adults, which is a population that is accustomed to the use of smartphones and Apps. Therefore, utilizing an App to report ADR could stimulate spontaneous reporting by patients.

According to data extracted on 15 December 2016 from the French MS Observatory “Observatoire Français de la Sclérose en Plaques (OFSEP)” based on an analysis of the French patient cohort EDMUS (http://www.ofsep.org/fr/la-cohorte-ofsep/descriptif-de-la-cohorte), each year, 5000 new patients are diagnosed with MS in France. The distribution of the various forms of MS is as follows: 79% relapsing-remitting multiple sclerosis (RR-MS), 11% progressive MS and 10% a clinically isolated syndrome. This trial will focus on patients with RR-MS, as these patients are involved in the management and monitoring of their pathology, with a population of 3950 newly diagnosed individuals per year in France. Furthermore, we know that 25% of RR-MS patients do not receive DMD (extracted from OFSEP). Thus, approximately 3000 first-line DMD evaluated in RR-MS patients are introduced per year in France. First-line DMD include interferon β, peginterferon β, glatiramer acetate, teriflunomide, and dimethyl fumarate.

#### Intervention

All patients included in Vigip-SEP will be informed that they can report their ADR using a pharmacovigilance system. They will also be informed of the existence of the App My eReport France® developed to report ADR in accordance with European and French regulations. In experimental centers, patients will be introduced to its use by neurologists. In control centers, they will not be introduced to its use but will be encouraged to report ADR through usual reporting methods.

The My eReport France® application was chosen for the Vigip-SEP study, developed by the eVeDrug® society, to report ADR to the appropriate French authorities in E2B language, in accordance with European regulations. The application is certified by the label “My health quality.” Data hosting is provided by a certified health data host. Updates are performed automatically according to the evolution of E2B regulations.

#### Comparison

The mean number of ADR per patient at the center will be compared between interventional and control centers.

#### Outcome

The principal aim of the Vigip-SEP study is to validate a proof-of-concept: Does the use of a mobile application (App) increase ADR reporting in RR-MS patients receiving first-line DMD?

## Methods/design

### Aim, design and setting

The overall aim of our Vigip-SEP trial is to study reporting of ADR by RR-MS patients using a mobile application.

The first aim is to evaluate the increase in ADR reporting by mobile application use. The second aim is to evaluate the quality of patient reporting. We will also evaluate the effect of patient involvement in pharmacovigilance on physician reporting (boost effect). Additionally, the user-friendliness of the application will be assessed according to the patients’ satisfaction, the patients’ judgment of practicability, and the patients’ suggestions for improvements.

The designed study is a multi-centric, open cluster-randomized controlled trial.

The Vigip-SEP study is set in France. The trial sponsor is CHU de Caen, an academic hospital, responsible for protocol decisions and quality control. Coordination is provided by an investigative team of MS academic experts at the center of CHU de Caen.

This study was approved by the Ethics Committee of Nord-Ouest III with approval number 2016–42. The privacy of the participants and their personal medical records will be guaranteed by treating the data according to the French law n. 78–17 of 6 January 1978 and the “European Union Data Protection Directive (95/46/EC 24 October 1995).”

The approved version of Vigip-SEP is V3 29.11.2016; the recruitment began in June 2017, and the end date is anticipated in May 2018.

The sponsor CHU de Caen is responsible for reporting any protocol modifications to the centers, ethic committees and ANSM.

### Subjects

To be eligible for participation, subjects must meet the following defined inclusion criteria:Men or women aged ≥ 18 years with RR-MSPatients undergoing the initiation of a first-line DMD (interferon β, peginterferon β, glatiramer acetate, teriflunomide, and dimethyl fumarate). Patients without ulterior first-line DMD or patients benefiting from a change in treatment between first-line DMD (switch)Patients who have access to a smartphone, tablet or other computer device that can host the selected mobile applicationPatients benefiting from the French Social Security systemSatisfactory level of comprehension and expression in FrenchPatients who provided written informed consent

Subjects meeting any one of the following exclusion criteria may not be eligible to participate in the study:Patients with secondary or primary progressive MSPatients with MS who are not being treated with a first-line DMD

### Description of all processes (see Fig. 1)

#### Randomization

The biostatistician of the sponsor CHU de Caen will perform the randomization. Randomization will be performed using the ALEA function of Microsoft Excel 2013.

**Fig. 1 Fig1:**
[figure not shown]
Enrollment, interventions and assessments in the Vigip-SEP study

Centers will be stratified based on structure type then randomly allocated (1:1) to the experimental arm (these centers will introduce all patients to use of the App) or to the control arm (these centers will not introduce patients to use of the App). Centers will be informed of the randomization the day of the trial initiation visit.

Clustering avoids a “contamination” bias (in the epidemiological sense) of different patients followed by the same prescriber.

Neurologists will successively include all patients meeting the criteria until they have reached the number of subjects to be included. In 1 year, MS academic expert centers are expected to include 10 patients, and general hospitals and private practice neurologists are expected to include 5 patients. Neurologists will inform patients about the Vigip-SEP study and obtain the patients’ written informed consent.

CHU de Caen conforms to National Informatic and Liberty French Law and, therefore, patient confidentiality will be protected.

#### Intervention arm

In the experimental arm, the patient is introduced to use of the App by a neurologist.

A video tutorial created by the investigator’s staff of the Vigip-SEP study is presented to the patient.

The patient is able to report his ADR via the mobile application. The report is electronically sent directly to the regional pharmacovigilance center, which assesses the case, and after treatment, records it in the national competent authority database in the usual manner.

Patients can also describe their ADR to their physician during consultation. A physician who is informed of an ADR by his patient is able to report it as usual (via the mobile application or via the conventional methods of reporting), and duplicate reports will be identified a posteriori.

A follow-up questionnaire will be administered to patients by telephone call during the study at 1 month (± 15 days). The patient will be asked if they had ADR and, if so, whether they reported the ADR and how. Education regarding the application will be monitored, and the user-friendliness of the application will also be evaluated by the patients’ satisfaction, practicability and suggestions.

#### Control arm

In the control arm, no intervention is performed except for follow-up questionnaires at 1 and 6 months. The patient is informed of the existence of the App but is not introduced to its use. The patient reports ADR according to the usual reporting procedures.

In both arms, any concomitant care is allowed. Usual care will be conducted in the post-trial period.

### Outcome measurements

#### Primary outcomes

The primary outcome is the number of ADR patient reports. ADR reports will be collected in both arms for 6 months after the inclusion of each patient from the national database of French authority, ANSM (see “Data collection procedure” below).

An example of the method of aggregation is as follows. For center 1, *m*1 = *n*1 reports/*N*1 patients, where *n*1 is the number of ADR in the center, and *N*1 is the number of patients included in the center.

The method of aggregation in each group follows the formula Ʃ*mx*/*N*, where *N* is the number of centers in the group.

#### Secondary outcomes

Each reaction is assessed by a regional pharmacovigilance center with a MedDRA coding. The profile of the ADR per drug classified by System Organ Class will be compared with the safety post-marketing profile in the Summary of Product Characteristics.

The number of physician reports will be compared between the two arms to measure the “boost” effect of patient reporting via the mobile application.

The user-friendliness of the application will be evaluated by analyzing the responses to the questionnaire completed at 1 month (± 15 days).

The feedback from the regional pharmacovigilance center will be evaluated by analyzing the responses to the questionnaire completed at 6 months (± 15 days).

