#### Data collection procedure

The data manager of CHU de Caen is responsible for form development, sponsor database development and data management.

Regardless of how ADR are reported, they are sent to a regional pharmacovigilance center for assessment, which includes MedDRA coding and causality analysis. Then, the regional pharmacovigilance center records the ADR in the national database.

At the end of the study, the 31 regional centers of pharmacovigilance will anonymously extract ADR reports pertaining to the first-line DMD in the trial period from the national database. The investigator’s team will identify reports of the Vigip-SEP population (of the two groups), and the Vigip-SEP investigators will compare the received date and the region, age and sex of the patient. ADR reported by patients within the 6 months of inclusion and by neurologists within the same period will be recorded in the sponsor database. Duplicates (the same ADR reports made by patients and physicians) will then be identified.

Data collected regarding the investigating centers will include the following:Type of structure: MS academic expert center, general hospital, private practice neurologistDate and result of randomizationDate of implementationRegional pharmacovigilance center attached to the investigating center

Data collected regarding patients will include the following:Socio-demographic information: patient initials, date of birth and genderConfirmation of diagnosis of RR-MS and date of diagnosisEDSS (Expanded Disability Status Scale) score at the time of inclusionDate of inclusionName and date of initiation of first-line DMD prescribedName of previous first-line DMD if the patient is not naïve of any MS treatmentIf a switch occurred in MS treatments during the course of the study, date of the current first-line DMD discontinuation and name and date of initiation of the new first-line DMDAdverse events: method of reporting, description, date, first-line DMD concerned, MedDra code, and expectedness (a previously known adverse reaction and its frequency, listed in the summary of the product characteristics of the drug)Responses to the questionnaire at 1 month (± 15 days), ADR, method of reporting, and friendliness of App (only in the experimental arm)Response to the questionnaire at 6 months (± 15 days) regarding feedback from the regional pharmacovigilance center

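### The between-arm difference in physician reports is the total effect of the App-introduction programme; it cannot be read as the boost effect of patient reporting

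*Protocol article*

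**What the plan says.** The aim is set in the protocol article under Aim, design and setting: "We will also evaluate the effect of patient involvement in pharmacovigilance on physician reporting (boost effect". Secondary outcomes turns it into a measure: "The number of physician reports will be compared between the two arms to measure the “boost” effect of patient reporting via the mobile application". Both passages treat the arm difference as something caused by patients.

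Other sections describe what the two arms receive and whose reports are kept:

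- **Intervention arm:** "In the experimental arm, the patient is introduced to use of the App by a neurologist". A physician told of a reaction by a patient "is able to report it as usual (via the mobile application or via the conventional methods of reporting".
- **Control arm:** "In the control arm, no intervention is performed except for follow-up questionnaires at 1 and 6 months".
- **Randomization (text beside Figure 1):** "Centers will be informed of the randomization the day of the trial initiation visit". The trial is open.
- **Data collection procedure:** "ADR reported by patients within the 6 months of inclusion and by neurologists within the same period will be recorded in the sponsor database".

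The same Data collection section plans to flag duplicate patient and physician reports and to collect the date and reporting method of each adverse event.

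**The concern.** Randomization assigns centers to a programme, not to patient reporting. That programme is delivered by the neurologists, and neurologists' reports are what the boost outcome counts. Someone who repeatedly demonstrates a reporting tool, and may use it, could report more on his or her own account. A higher physician count in the App arm could then be published as patients stimulating physicians when it shows, wholly or partly, that the neurologists themselves were engaged.

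Whose reports count is also unclear. Secondary outcomes speaks of physician reports, while the Data collection procedure records those of neurologists. If the second wording is literal, reports from other physicians are lost. Those physicians do not deliver the App introduction, so a boost among them would be harder to explain by a direct effect of the study.

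**Working it through.** **What the contrast contains.** The document gives no target figure for the boost outcome, so there is none to reproduce. The passages are taken in order:

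1. The quantity claimed is the path from patient report to physician report (Aim, design and setting; Secondary outcomes).
2. The quantity randomized is the App introduction, given by neurologists in one arm and absent in the other (Intervention arm; Control arm).
3. The reporters counted are neurologists (Data collection procedure).
4. Arm difference = direct effect on neurologists + effect through patients' reports. Nothing in Secondary outcomes separates the two terms.
5. The hierarchical models in the Statistical analysis plan section adjust for clustering and for confounders at patient and physician level. Delivering the App introduction coincides with the arm, so such adjustment cannot remove it.

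**Size, as an illustration.** Inputs:

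- 90 patients per arm (Hypothesis). This agrees with the center mix: 6 × 10 + 3 × 5 + 3 × 5 = 90.
- 271 physician reports in 2015 (Discussion).
- 3000 patients, the denominator that Hypothesis uses for patient reports. Applying it to physician reports is an assumption.
- 200/3000 patient reports per patient in the App arm (Hypothesis).

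Expected physician reports per arm: 90 × 271/3000 = 8.13. If the annual rate is halved for a 6-month window: 4.07.

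Suppose the App arm shows twice the control count. With total ratio = direct ratio × patient-driven ratio:

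| Direct ratio | Patient-driven ratio | Control arm | App arm |
|---|---|---|---|
| 2 | 1 | 8.13 | 16.26 |
| 1 | 2 | 8.13 | 16.26 |
| 1.414 | 1.414 | 8.13 | 16.26 |

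The three rows give the same data.

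A second illustration uses the protocol's own expected patient reports: 90 × 200/3000 = 6.0 in the App arm. If each prompted one extra physician report (assumed), the counts would be 8.13 + 6.0 = 14.13 against 8.13. A purely direct ratio of 14.13/8.13 = 1.74 would give the same counts. Assumed direct ratios of 1.25, 1.5 and 2 with no boost add 2.0, 4.1 and 8.1 reports, which is 34%, 68% and 136% of the 6-report boost. No passage supports a particular ratio; the range shows only that a moderate direct effect would be of the same order as the signal sought.

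The counts are also small. An exact two-sided 5% comparison of 14.13 with 8.13, ignoring clustering, has power of about 0.18 (0.08 with halved rates). That is a separate limitation from attribution, but it bears on how much any descriptive table can show.

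**The case against.** A reader might infer that the comparison measures the direct effect on neurologists and nothing of the boost, or that it is bound to be positive. The documents support neither. Any patient-driven effect is inside the randomized difference and is only inseparable from the rest. No passage demonstrates a direct effect that differs by arm.

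The over-reporting conceded under Hypothesis and under Strengths and limitations might be read as evidence of such an effect. It is not. Both passages describe the effect of informing people about the study, without saying that it differs by arm. Control neurologists also know of the study, tell patients that the App exists, and encourage reporting by the usual routes (Background, Intervention). The contrast in engagement is one of degree.

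It is also tempting to say that only trial neurologists' reports are kept. The Data collection procedure says neurologists, without qualification. Its next sentences, the Intervention arm section and Secondary outcomes say physicians, and the extraction covers all reports on first-line DMD. Loose wording in a condensed article is as plausible as deliberate exclusion, so what stands is that the terms must be reconciled.

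Finally, dates, methods and duplicates are already planned, and their detailed use may be set out in a full protocol or analysis plan that is not shown. That is fair as to method. It does not answer the main point, because the article itself already fixes the interpretation of the contrast.

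**Conclusion.** The concern holds as a matter of attribution. The comparison is a valid estimate of what the App-introduction programme does to physician reporting, by all routes together. It does not isolate the effect of patient reporting, and a positive difference could arise with no patient-driven boost. The passages naming physicians and neurologists also need to be reconciled.

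This conclusion rests on the structure of the design and not on the numerical illustration. The figure of about 8 physician reports per arm (about 4 if halved) assumes that 271/3000 applies to trial patients. The 271 reports concern first-line DMD in general, whereas 3000 is the yearly number of introductions. The direct ratios are assumed as well. The outcome is secondary and the primary result is unaffected, but the correction changes what the trial may conclude about its boost aim.

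**What to change.** 1. **Secondary outcomes, and the matching aim.** Describe the contrast as the total effect of the App-introduction programme on physician reporting, and do not attribute it to patient reporting.
2. **Data collection procedure.** Reconcile it with Secondary outcomes so that reports by all physicians for trial patients are recorded, with reporter type (trial neurologist or other physician).
3. **Exploratory description only.** Tabulate by arm the reports from other physicians, and the physician reports that follow, duplicate or occur without a report by the same patient. Use the dates, reporting methods and duplicate flags already planned; the order of reports should rest on the date received, which is already used for matching. State that a later physician report does not prove stimulation, because the patient may simply have described the same reaction at a consultation.

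The cost is a wording change, one coded field and one descriptive table, with no extra patients or visits. The article does not say whether the national extraction identifies the type of physician, so this should be checked first. The downside is that the boost claim becomes narrower and rests on few reports.
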